# Efficacy of WuSheZhiYang Pills in Mild-to-Moderate Atopic Dermatitis: Protocol for a Double-Blind, Randomized, Placebo-Controlled Trial

**DOI:** 10.2196/77927

**Published:** 2025-07-02

**Keywords:** atopic dermatitis, WSZY pills, randomized controlled trial, clinical trial protocol, skin diseases

## Abstract

**Background:**

Atopic dermatitis (AD) is a recurrent, inflammatory, and chronic skin disease that influences over 200 million individuals around the world and is viewed as an important health problem due to its elevated prevalence, long course of disease, and heavy disease burden. WuSheZhiYang (WSZY) pills are composed of 11 Chinese herbs and have the effects of nourishing the blood, drying dampness, and relieving itching. In clinical practice, WSZY pills are recommended for itching skin diseases, but high-quality clinical trial evidence is still limited.

**Objective:**

In this study, we will implement a double-blind, randomized, placebo-controlled trial to evaluate the efficacy of WSZY pills for mild-to-moderate AD. We hypothesized that WSZY pills can effectively alleviate the disease condition of patients with mild-to-moderate AD.

**Methods:**

In this study, we will recruit 60 patients with mild-to-moderate in Shanghai Skin Diseases Hospital from December 2024 through December 2025. In this study, 60 male and female patients with AD aged 18 years to 65 years will be randomly assigned (2:1) to the treatment group (urea ointment and WSZY pills; n=40) or control group (urea ointment and placebo WSZY pills; n=20), and both groups will receive 4 weeks of treatment and 4 weeks of follow-up. The treatment group will receive 3 sessions of urea ointment and 7.5 g of WSZY pills each day for 4 weeks, and the control group will also receive 3 sessions of urea ointment and 7.5 g of placebo WSZY pills each day for 4 weeks. The primary indicator is the change in the objective Scoring Atopic Dermatitis (SCORAD) score between baseline and week 4. The secondary indicators include SCORAD at week 2 and week 8; Peak Pruritus Numerical Rating Scale (PP-NRS), Investigator's Global Assessment (IGA), Patient-Oriented Eczema Measure (POEM), and Dermatology Life Quality Index (DLQI) at week 2, week 4, and week 8; and the proportion of participants receiving remedial treatment, amount of levocetirizine tablets used, and recurrence rate at week 8. In this study, we will analyze the full analysis set and per-protocol set using SAS software version 9.4, and a 2-tailed alpha level of .05 will be viewed as statistically significant.

**Results:**

The study received ethics permission in September 2024, and trial registration was completed in October 2024. Recruitment started in December 2024 and is expected to be completed by December 2025. As of June 2025, 30 participants with mild-to-moderate AD were enrolled. Data analysis will begin in January 2026. The main results of the trial are expected to be submitted for publication in peer-reviewed scientific journals in the summer of 2026.

**Conclusions:**

This study will evaluate the efficacy of WSZY pills for AD and provide additional evidence, suggest new therapeutic options for patients, and reduce their disease burden.

**Trial Registration:**

International Traditional Medicine Clinical Trial Registry ITMCTR2024000724; http://itmctr.ccebtcm.org.cn/zh-CN/Home/ProjectView?pid=bda070f8-a733-4f52-87b0-39e4be57ac00

**International Registered Report Identifier (IRRID):**

DERR1-10.2196/77927

## Introduction

### Background

Atopic dermatitis (AD), a chronic inflammatory skin disorder characterized by chronic eczematous lesions and intense pruritus, affects more than 200 million individuals worldwide [1]. Although the prevalence of AD in China has increased later than in western higher-income countries, it has increased rapidly in the past 10 years. Globally, AD is associated with a heavy disease burden, and it is the skin disease with the highest disease burden among nonfatal diseases [2]. AD has become an important health problem due to its elevated prevalence, long course of disease, and heavy disease burden.

AD can cause not only skin lesions, itch, pain, and sleep disorders but also a heavy psychological burden. Clinical practice often aims to alleviate clinical symptoms, reduce recurrence, reduce complications, and improve life satisfaction in patients [3]. Many treatment methods for ADs have been proposed, such as emollients containing urea, antihistamines, corticosteroids, antimicrobial agents, and immunotherapy [4-6]. Corticosteroids are the main treatment method, but their use is limited due to the susceptibility to cause adverse reactions [7-11].

Traditional Chinese medicine (TCM) has been systematically used in AD treatment and management and has shown good effects at alleviating the disease condition, reducing disease recurrence, improving quality of life, and causing fewer adverse reactions [12]. WuSheZhiYang (WSZY) pills, part of TCM, are composed of 11 herbs, including *Zaocys dhumnades*, *Saposhnikovia divaricata*, snake bile, cortex *Phellodendri amurensis*, rhizoma atractylodis, radix ginseng, fructus cnidii, *Sophora flavescens*, artificial bezoar, and *Angelica sinensis*. They are used orally and have the effects of nourishing the blood, dispelling wind, drying dampness, and relieving itching. Nourishing the blood means that it improves skin dryness and desquamation caused by blood deficiency; dispelling wind means that it evacuates pathogens, reduces skin irritation caused by pathogens, and alleviates pruritus; drying dampness means that it clears heat and eliminates dampness in the body to reduce eczema exudation; and relieving itching means that it directly inhibits itching symptoms caused by pathogens. WSZY pills are usually prescribed for patients with mild-to-moderate itching skin diseases (eczema, urticaria, pruritus, neurodermatitis, seborrheic dermatitis, pityriasis rosea, psoriasis vulgaris) in clinical practice but without high-quality clinical trial evidence for mild-to-moderate AD. Therefore, we will carry out exploratory research with patients with mild-to-moderate AD.

### Objectives

In this study, we plan to implement a double-blind, randomized, placebo-controlled clinical trial to evaluate the efficacy of WSZY pills for mild-to-moderate AD. Our primary objective is to evaluate the effect of WSZY pills on the severity of AD and recurrence rates in patients with mild-to-moderate AD. The secondary objectives are to assess the effect of WSZY pills on itching level, quality of life, and safety in patients with mild-to-moderate AD. This trial will provide additional evidence for the clinical efficacy of WSZY pills for AD treatment, which may provide a new treatment option for patients with mild-to-moderate AD. We hypothesized that WSZY pills can effectively alleviate the disease condition of patients with mild-to-moderate AD.

## Methods

### Study Design

This study is a double-blind, randomized, placebo-controlled trial to evaluate the efficacy of WSZY pills for AD treatment. It was designed in line with the SPIRIT (Standard Protocol Items: Recommendations for Interventional Trials) statement [13]. Patients with mild-to-moderate AD will be recruited in inpatient and outpatient departments in Shanghai Skin Disease Hospital from December 2024 through December 2025. In this study, 60 patients with mild-to-moderate AD will be randomly assigned (2:1) to the treatment group (urea ointment and WSZY pills; n=40) or control group (urea ointment and placebo WSZY pills; n=20). All participants in both groups will undergo a 4-week treatment phase followed by a 4-week observational follow-up to evaluate the treatment response and disease progression. The flowchart of this study is shown in Figure 1.

**Figure 1 figure1:**
[figure not shown]
Clinical trial flowchart. AD: atopic dermatitis; DLQI: Dermatology Life Quality Index; IGA: Investigator's Global Assessment; POEM: Patient-Oriented Eczema Measure; PP-NRS: Peak Pruritus Numerical Rating Scale; SCORAD: Scoring Atopic Dermatitis; TCM: traditional Chinese medicine; WSZY: WuSheZhiYang.

### Inclusion Criteria

The inclusion criteria in this study are as follows: (1) patients diagnosed with AD according to the Williams diagnostic criteria [14], (2) patients with AD meeting the definition of blood deficiency and wind dryness in TCM [15], (3) patients with mild-to-moderate AD (objective Scoring Atopic Dermatitis [SCORAD] score ≤50, body surface area ≤10%), (4) male or female patients aged 18 years to 65 years, and (5) signed informed consent forms.

The main Williams diagnostic criterion is skin itching, while the secondary criteria are (1) a history of dermatitis and eczema on the flexed side, including the elbow fossa, popliteal fossa, ankle anterior, and neck; (2) history of asthma or allergic rhinitis; (3) history of dry skin on the entire body in recent years; (4) eczema on the flexor side (eczema on the cheeks or forehead and extensor sides of the limbs in children younger than 4 years), and (5) onset before the age of 2 years (for patients older than 4 years) [14]. A confirmed diagnosis for AD involves meeting the main criterion plus 3 or more of the secondary criteria.

### Exclusion Criteria

In this study, the exclusion criteria include (1) patients with AD who have severe cardiovascular or cerebrovascular disease or tumors; (2) patients with abnormal laboratory indicators (serum creatinine, aspartate aminotransferase, alanine aminotransferase, gamma glutamyl transpeptidase, alkaline phosphatase, and total bilirubin); (3) patients treated with glucocorticoids or immunosuppressants within the last 2 weeks; (4) patients treated with biologics within the last 3 weeks; (5) patients receiving TCM judged to affect the efficacy evaluation within the last 1 week; (6) patients who are allergic to the intervention drug components; (7) patients who are pregnant, breastfeeding, or planning to become pregnant; and (8) patients who participated in other clinical trials within the last 3 months.

### Sample Size

In this study, the sample size was calculated based on the difference in the change in SCORAD score from baseline (week 0) to week 4, as the primary indicator, between the treatment group (urea ointment and WSZY pills) and control group (urea ointment and placebo WSZY pills). Based on previous evidence on the efficacy of TCM for AD treatment, we used a difference of 9.8 (SD 12) points [16]. ‌Sample size estimation‌ was performed using PASS 15.0 software (NCSS Statistical Software). Using the SD of 12.0, the sample size calculation for the 2:1 randomization design indicated that 36 patients with AD in the treatment group and 18 patients with AD in the control group would provide 80% statistical power to detect a difference of 9.8 points in the improvement in the SCORAD score at a 2-tailed α level of .05. Considering a dropout rate of 10%, we plan to enroll 40 patients with AD and 20 patients with AD in the treatment group and control group, respectively.

### Randomization

In this study, patients with AD will be randomly allocated at a 2:1 ratio to either the treatment group or the control group. We will use cluster randomization with combined blocks of 4 and 6 to ensure a balanced group allocation. An independent statistician will construct the computer-generated randomization sequences using SAS software (version 9.4; SAS Institute Inc). To ensure allocation concealment, the generated allocation schedules will be sealed in sequentially numbered, light-resistant envelopes and securely maintained by an independent trial coordinating center.

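### Blocks of 4 cannot hold the stated 2:1 allocation, and *cluster* contradicts the patient-level randomisation described everywhere else

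*Protocol article*

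**What the plan says.** The Randomization section of the protocol article first sets the unit and the ratio: "patients with AD will be randomly allocated at a 2:1 ratio to either the treatment group or the control group". Its next sentence gives the method: "We will use cluster randomization with combined blocks of 4 and 6 to ensure a balanced group allocation". An independent statistician generates the sequence, and an independent coordinating centre keeps it in sealed, numbered envelopes.

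The Abstract and Study Design give the target as 60 patients, 40 on treatment and 20 on control. The Sample Size section works at patient level: "we used a difference of 9.8 (SD 12) points", and "36 patients with AD in the treatment group and 18 patients with AD in the control group would provide 80% statistical power". It then allows for losses: "Considering a dropout rate of 10%, we plan to enroll 40 patients with AD and 20 patients with AD".

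The article defines no cluster, intracluster correlation or cluster-adjusted analysis. Limitations confirms that all patients come from one hospital, and Statistical Analysis compares patients by t, Wilcoxon, chi-square or Fisher tests. The composition of the blocks of 4 is not given.

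**The concern.** Two statements in one sentence do not fit the rest of the design.

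- **Block size.** A permuted block keeps a 2:1 ratio only if its size is divisible by 3. Six qualifies and four does not. Followed as written, the scheme does not in general produce the 40:20 split that the article states and from which its 36:18 evaluable numbers derive.
- **Unit of randomisation.** Cluster randomisation means allocating groups of patients together. That is a different design, with a different sample size calculation and a different analysis.

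At stake are the realised ratio and a correct public record of how patients were allocated. The point is timely: Results reports 30 participants enrolled by June 2025, half the target, and Table 1 places randomisation at the baseline visit.

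**Working it through.** **Inputs.** Ratio 2:1, block sizes 4 and 6 (Randomization); 60 patients, 40:20 (Study Design); difference 9.8, SD 12, two-sided α 0.05, 36:18 evaluable, 10% dropout (Sample Size).

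**1. The plan's own figures.** For a two-sample t test the noncentrality is δ / [SD × √(1/n₁ + 1/n₂)].

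- At 36:18: 9.8 / [12 × √(1/36 + 1/18)] = 9.8 / 3.464 = 2.829, with 52 degrees of freedom. Power is 0.793 by the noncentral t and 0.808 by the normal approximation.
- Dropout: 36 / 0.9 = 40 and 18 / 0.9 = 20.

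The stated 80% and the enrolment of 40 and 20 both reproduce.

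**2. What each block can hold.** Two thirds of 6 is 4, so a block of 6 is 4:2. Two thirds of 4 is 2.67, so a block of 4 with both arms present is 3:1, 2:2 or 1:3. The two nearest to 2:1 are 3:1 and 2:2.

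**3. Which lists of 60 are possible.** With *a* blocks of 4 and *b* blocks of 6, 4a + 6b = 60. Using both sizes, *a* must be 3, 6, 9 or 12. The treatment arm is 3a + 4b if the 4s are 3:1, and 2a + 4b if they are 2:2. Power is by the noncentral t after each arm is multiplied by 0.9.

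| Blocks of 4 / of 6 | 4s at 3:1 | Power | 4s at 2:2 | Power |
|---|---|---|---|---|
| 3 / 8 | 41:19 | 0.782 | 38:22 | 0.810 |
| 6 / 6 | 42:18 | 0.770 | 36:24 | 0.823 |
| 9 / 4 | 43:17 | 0.756 | 34:26 | 0.831 |
| 12 / 2 | 44:16 | 0.740 | 32:28 | 0.836 |

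No row gives 40:20, for which the power after dropout is 0.793.

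**4. The equal mix in full.**

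- 42:18 becomes 37.8:16.2, with noncentrality 9.8 / [12 × √(1/37.8 + 1/16.2)] = 2.750 and power 0.770.
- 36:24 becomes 32.4:21.6, with noncentrality 9.8 / [12 × √(1/32.4 + 1/21.6)] = 2.940 and power 0.823.
- Against 0.793, the changes are −0.023 and +0.030.
- With all 60 analysed, power is 0.813 or 0.862, against 0.835 at 40:20.

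**5. Random block sizes.** In 20,000 simulated lists, with sizes 4 and 6 assumed equally likely and the list cut at 60, the treatment arm averaged 42 (95% range 41 to 44) for 3:1 and 36 (33 to 38) for 2:2. Exactly 40:20 occurred in about 2% and 0.5% of lists.

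**6. Multiples of 3.** A complete list of 60 in blocks of 3 (2:1) and 6 (4:2) gives exactly 40:20, so the sample size and its power do not change.

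**The case against.** The best defence is that this is a faulty sentence in an article, not a demonstrated fault in the trial. Much of that stands.

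- **The list itself.** The article cannot show whether blocks of 4 were ever used or whether the sentence misreports a sound list.
- **Varying composition.** Blocks of 4 could average 2:1 if two 3:1 blocks were used for each 2:2 block (3 + 3 + 2 = 8 of 12). This is possible, but the article describes no such rule.
- **Power.** A reader might infer that the 80% power fails. It does not. The calculation reproduces, and the realised power could move either way. A figure near 72% (0.7225, from 45:15 after dropout) needs every block to be a 4 split 3:1, which is not the stated mix.
- **Clusters.** A reader might infer that the t tests and sample size are invalid. That requires *cluster* to be literal. Purely for illustration, assumed clusters of 5 with intracluster correlation 0.01 to 0.10 give design effects 1 + 4 × ICC of 1.04 to 1.40, and power at 36:18 of about 0.78 to 0.64. Nothing else in the article supports clusters, and the preceding sentence allocates patients.
- **Validity.** A ratio of 2.3:1 or 1.5:1 does not in itself bias the comparison, and concealment and blinding are not called into question here.

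What the defence does not answer is that the sentence, as published, cannot be reconciled with the article's own ratio or unit of randomisation. This is not detail left to a fuller document: the scheme is stated, and stated wrongly.

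**Conclusion.** The point holds in a limited form. Blocks of 4 are incompatible with an exact 2:1 split. With one fixed composition for the 4s, every complete-block mix of 4s and 6s totalling 60 misses 40:20, by 1 to 4 patients in the treatment arm at 3:1 and by 2 to 8 at 2:2. *Cluster* is contradicted by the rest of the article and is most likely an error for *block*.

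The statistical consequence is small. For equal numbers of each block size, power shifts by about −2 to +3 percentage points. The sign is unknown because the composition of the 4s is not stated. These figures assume the plan's difference and SD, a two-sided t test and 10% loss in each arm. The sample size calculation needs no change.

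**What to change.** - **Correct the sentence.** State individual permuted-block randomisation with block sizes that are multiples of 3 (for example 3 and 6), and delete *cluster*.
- **Check the issued list.** The independent holder of the list should establish which block sizes were used. The trial statistician should not do this, because the Blinding section keeps that role blinded throughout.
- **If blocks of 4 were used,** leave issued assignments unchanged, build the rest of the list from multiples of 3, and report the actual scheme and realised ratio. This stops further drift but will not generally restore 40:20.
- **If they were not,** correcting the published sentence is enough.

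The cost is one sentence, one check by the list-holder and at most a regenerated remainder of the list. No patients are added.

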### Blinding

In this study, patients with AD, dermatologists (investigators), data collectors, and the statistician will be blinded to the treatment allocation during the entire trial period to prevent bias. Rigorous allocation concealment is preserved through physical separation of randomization records from study operations. This comprehensive blinding strategy aims to mitigate bias during delivery of the intervention, endpoint evaluation, and statistical interpretation.

### Interventions

In this study, patients with AD in the treatment group will receive 3 sessions of urea ointment and 7.5 g of WSZY pills each day for 4 weeks. To ensure the correct application of urea ointment, we will instruct the patients to apply urea ointment to the affected area and instruct patients that one knuckle length of urea ointment should be used to cover no more than 1% of the body surface area. This should be followed by a finger massage of the area for 3 minutes to 5 minutes to promote absorption. To ensure the correct administration of WSZY pills, we will instruct patients to take 1 bag (2.5 g) of the WSZY pills per dose, 3 times a day with water.

Patients with AD in the control group will also receive 3 sessions of urea ointment and 7.5 g of placebo WSZY pills each day for 4 weeks. The placebo WSZY pills are made of dextrin and are produced and provided by the same company, which maintains complete consistency with the WSZY pills in terms of appearance, weight, color, odor, and package. The application, individual guidance, and instruction for placebo WSZY pill administration among patients in the control group is completely in line with that in the treatment group.

In this study, patients will be instructed not to use any additional treatment for AD. If a patient uses additional treatment for an emergency condition, detailed information should be recorded, and the patient should be withdrawn.

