### Outcomes

#### Primary Outcome

The primary outcome indicator in this study is the difference in the SCORAD score change from baseline (week 0) to week 4. The SCORAD index is made of the affected body surface area, skin lesion severity, and patient self-assessment of itching and quality of sleep. It is an evaluation method to assess the severity of AD as objectively as possible.

The SCORAD score includes the doctor's assessment (A, B) and the patient's own assessment (C), which is the most comprehensive evaluation method. (A) involves evaluating the affected area, including the head and neck area (accounting for 9%), both upper limbs (accounting for 9% each), both lower limbs (accounting for 18% each), the front and back of the trunk (accounting for 18% each), and the genital area (accounting for 1%). (B) involves 6 clinical features, including erythema, edema or papules, exudation or scabbing, epidermal peeling, lichenification, and dryness. Each feature is scored according to its severity, ranging from 0 to 3 points for each item. The patient self-assessment (C) includes itching and sleep deprivation in the last 3 days. The SCORAD score is calculated as A/5+7×B/2+C, with the total score ranging from 0 to 103 points. A higher score indicates a more severe disease condition. According to the score, the condition is considered mild (0-24 points), moderate (25-50 points), or severe (>50 points) [17]. In this study, the SCORAD will be estimated at baseline (week 0), week 2, week 4, and week 8.

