#### Secondary Outcomes

##### Overview

The secondary outcome indicators include the SCORAD score at week 2 and week 8; Peak Pruritus Numerical Rating Scale (PP-NRS), Investigator’s Global Assessment (IGA), Patient-Oriented Eczema Measure (POEM), and Dermatology Life Quality Index (DLQI) at week 2, week 4, and week 8; and the proportion of participants receiving remedial treatment, the amount of levocetirizine tablets used, and the recurrence rate at week 8 [18,19]. A comprehensive study schedule is provided in Table 1, and details of secondary outcome indicators are included.

**Table 1 table1:** Study schedule of the WuSheZhiYang (WSZY) pill clinical trial (8 weeks).

Indicator	Baseline	Treatment		Follow-up
	Visit 1 (week 0)	Visit 2 (week 2)	Visit 3 (week 4)	Visit 4 (week 8)
Informed consent	✓	—^a^	—	—
Demographic feature	✓	—	—	—
History of surgical treatment	✓	—	—	—
History of disease	✓	—	—	—
Vital sign	✓	✓	✓	✓
Physical examination	✓	—	✓	—
Pregnancy examination	✓	—	—	✓
Inclusion/exclusion criteria check	✓	—	—	—
Randomization	✓	—	—	—
SCORAD^b^	✓	✓	✓	✓
PP-NRS^c^	✓	✓	✓	✓
IGA^d^	✓	✓	✓	✓
POEM^e^	✓	✓	✓	✓
DLQI^f^	✓	✓	✓	✓
Proportion of participants receiving remedial treatment	—	—	—	✓
Levocetirizine tablets used	—	—	—	✓
Recurrence rate	—	—	—	✓
Routine blood tests	✓	—	✓	—
Route urine tests	✓	—	✓	—
Blood biochemistry	✓	—	✓	—
Electrocardiogram	✓	—	✓	—
Drug use history	—	✓	✓	—
Concomitant medications	—	✓	✓	✓
Adverse events	—	✓	✓	✓

^a^Not applicable.

^b^SCORAD: Scoring Atopic Dermatitis.

^c^PP-NRS: Peak Pruritus Numerical Rating Scale.

^d^IGA: Investigator’s Global Assessment.

^e^POEM: Patient-Oriented Eczema Measure.

^f^DLQI: Dermatology Life Quality Index.

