### Statistical Analysis

All data will be systematically recorded in the CRF and subsequently entered into a dual-validated electronic database using EpiData software 3.1, with final analyses performed using SAS 9.4. Quantitative variables that are normally distributed will be described using mean and SD, and those a skewed distribution will be described using median and interquartile range. Student *t* tests or Wilcoxon rank-sum tests will be used to compare the differences between groups for quantitative variables as appropriate, depending on the data distribution. Categorical variables will be presented as frequencies and proportions (%), and chi-square tests will be used to compare the differences in categorical variables between the groups. In addition, when the expected frequency is low (<1), Fisher exact tests will be used to compare the differences in categorical variables between the groups. In this study, a 2-tailed α level of .05 will be viewed as statistically significant. Statistical analyses will follow the intention-to-treat principle, including all randomly assigned patients regardless of protocol adherence or study completion [21]. We will handle missing data based on the assumption of missing-at-random and use the sequential regression multiple imputation method, which imputes missing values using regression models for each variable, conditional on the other variables in the data [22]. Additionally, analyses will be performed on both the full analysis set and the per-protocol set.

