## Discussion

### Summary

To our knowledge, this is the first clinical trial to use WSZY pills to treat AD. This study explores the efficacy of WSZY pills for AD treatment, with the goal of providing additional effective treatment recommendations. The expected results of this study are that the WSZY pills combined with urea ointment can effectively alleviate the disease condition of patients with mild-to-moderate AD.

AD is an itchy, inflammatory, and chronic skin dermatitis affecting both children and adults and is one of the most common chronic skin diseases [23,24]. AD usually exhibits a chronic course with thickening of skin, sleep disturbance, severe interference of quality of life, and impact on daily activities, which not only cause physical pain for patients but also impose heavy social and economic burdens [25]. Modern pharmacological studies indicate that the ingredients of WSZY pills have immunomodulatory and anti-inflammatory properties. For example, the water extracted from *Zaocys dhumnade* has immunomodulatory, anti-inflammatory, and capillary permeability–reducing effects. Oxymatrine in *Sophora flavescens* has immunosuppressive effects, and flavonoids and polysaccharides have anti-inflammatory effects [26,27]. Although the application of TCM has a long history in the treatment of AD in China, high-quality clinical trial evidence is still needed to demonstrate its efficacy and safety [2,28,29].

WSZY pills are part of TCM and have been used in clinical practice for more than 30 years. Previous studies have shown that the combination of WSZY pills and ebastine tablets can alleviate itching, can improve erythema and exudation, can reduce recurrence, and has a good safety profile [30]. In addition, the combination of WSZY pills and dehumidification Zhiyang ointment can improve acute eczema, alleviate the stimulating effect of inflammatory factors, reduce recurrence, and result in fewer adverse reactions [31]. Therefore, the risk associated with the intervention group receiving WSZY pills is limited. Moreover, basic treatment (urea ointment) and remedial treatment (if severe itching occurs, levocetirizine tablets will be administrated) are also included in the study design, which ensures the safety of all patients with AD enrolled in this study.

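### The rule withdrawing users of additional treatment has no stated exemption for the levocetirizine rescue built into the design; read literally, it ends outcome assessment for a reason linked to the outcome

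*Protocol article*

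**What the plan says.** All references are to the protocol article.

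- **Interventions.** The rule for participants is that "patients will be instructed not to use any additional treatment for AD". The consequence follows: "If a patient uses additional treatment for an emergency condition, detailed information should be recorded, and the patient should be withdrawn". Levocetirizine is not mentioned there, and the section does not say whether withdrawal means from study drug or from the study.
- **Discussion, Summary.** Urea ointment as basic treatment and "remedial treatment (if severe itching occurs, levocetirizine tablets will be administrated) are also included in the study design".
- **Secondary Outcomes, Overview** (and the Abstract). The secondary outcomes include "the proportion of participants receiving remedial treatment, the amount of levocetirizine tablets used, and the recurrence rate at week 8". Table 1 gives these three items a slot only at week 8. It lists concomitant medications at weeks 2, 4 and 8.
- **Primary Outcome.** "The primary outcome indicator in this study is the difference in the SCORAD score change from baseline (week 0) to week 4". On the composition of the score: "The patient self-assessment (C) includes itching and sleep deprivation in the last 3 days".
- **Statistical Analysis.** The analysis is by intention to treat and covers everyone randomised, whether or not they adhere or complete. On gaps: "We will handle missing data based on the assumption of missing-at-random", using sequential regression multiple imputation. A per-protocol analysis is added.

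**The concern.** Taking levocetirizine for severe itching is provided for in one section, counted as an outcome in another and, on the plain wording of a third, a reason for withdrawal. Investigators could apply this differently from patient to patient.

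The statistical stake is which data go missing and why. Severe itch triggers rescue, and itch is part of the primary score. Patients withdrawn for rescue before week 4 would therefore tend to be those doing badly, and their primary measurement would be replaced by a modelled value. An intention-to-treat analysis of everyone randomised is most convincing when outcomes are measured after such events. Nothing in the article says that assessments continue after withdrawal. Recurrence, which the Objectives section places within the primary objective, is scheduled only at week 8, so a withdrawn patient would not contribute it.

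**Working it through.** **1. Consequences under each reading.**

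| Reading | Week-4 SCORAD | Week-8 items | Levocetirizine amount | Proportion rescued |
|---|---|---|---|---|
| Levocetirizine counts as additional treatment; withdrawn means from the study | Not observed if rescue precedes week 4; already observed if rescue falls in weeks 4 to 8 | Not observed for any rescue user | Cut off at first use | Countable, because details are recorded at the event |
| Levocetirizine is exempt; withdrawn means from the study | Not observed for users of other emergency treatment before week 4 | Not observed for those users | Intact for patients who stay in | Countable |
| Withdrawn means from study drug only | Observable, if visits continue | Observable, if visits continue | Observable, if visits continue | Countable |

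The article does not say which reading applies. The first two lose data for a reason plausibly linked to the outcome. The third would not, but it is not stated.

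**2. What imputation can recover.** SCORAD, PP-NRS, IGA, POEM and DLQI are collected at baseline and week 2 (Table 1). The imputation conditions on other variables, so a patient withdrawn after week 2 is imputed using that patient's own earlier severity. It cannot see a flare that starts after the last visit and itself prompts the withdrawal. In that case missing-at-random is doubtful.

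**3. The plan's own sample size.** The inputs from Sample Size are "we used a difference of 9.8 (SD 12) points", two-sided alpha 0.05, 80% power, 2:1 allocation and 10% dropout.

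- Control n = (1 + 1/2) × (1.960 + 0.842)² × 12² / 9.8² ≈ 17.7, so 18, with 36 in the treatment group.
- Inflation: 36/0.9 = 40 and 18/0.9 = 20.
- Power at 36/18 is 80.8% by the normal approximation and 79.3% by the noncentral t.

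The stated figures reproduce, so there is no sample-size error here. The 10% allowance takes 60 enrolled exactly to 54 evaluable, with no reserve.

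**4. Illustration of power.** The rescue-withdrawal rates are assumed, because the article gives none. Observed n = enrolled × 0.9 × (1 − rescue share), for example 20 × 0.9 × 0.8 = 14.4 controls. Power is from the noncentral t with difference 9.8 and SD 12.

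| Control / treatment withdrawn for rescue | Observed control / treatment | Power |
|---|---|---|
| 0% / 0% | 18.0 / 36.0 | 79.3% |
| 10% / 5% | 16.2 / 34.2 | 75.6% |
| 20% / 10% | 14.4 / 32.4 | 71.3% |
| 30% / 15% | 12.6 / 30.6 | 66.4% |
| 40% / 20% | 10.8 / 28.8 | 60.6% |

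These figures describe observed cases only. They also assume that rescue withdrawals come on top of the 10%.

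**5. Illustration of bias after imputation.** Shift = (share withdrawn for rescue before week 4 in control − share in treatment) × points by which those patients are truly worse than imputed. With an assumed gap of 0.15 and 10 points, the shift is 0.15 × 10 = 1.5 points, or 1.5/9.8 ≈ 15% of the planned effect. Assumed gaps of 0.05 to 0.20 and 5 to 15 points give 0.05 × 5 = 0.25 to 0.20 × 15 = 3.0 points. If controls need more rescue, the shift is towards no effect.

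**The case against.** The best defence is that additional treatment means treatment outside the design. Levocetirizine is described as inside the design, and counting tablets to week 8 makes sense only if users stay in. That is a fair reading and may be the intended one. It is not written down, however, and it leaves users of other emergency treatment withdrawn.

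A reader might also infer stronger claims that the documents do not support:

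- **That the rules cannot be reconciled at all.** A sentence of clarification could reconcile them.
- **That every rescue user loses the primary value.** Only rescue before week 4 does this.
- **That lost values are imputed as if from patients without trouble.** The model conditions on baseline and any week-2 data.
- **That the rescue proportion becomes uninterpretable.** Withdrawal for rescue itself identifies the user, details must be recorded, and concomitant medications are collected at three visits. Only the amount is truncated.
- **That a known amount of power or a known bias follows.** No rescue rate is given, imputed patients remain in the planned analysis, and the article does not say that its 10% excludes such withdrawals. A rescued patient 10 points worse than imputed would exceed the whole planned difference of 9.8.

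It is also fair that, under the assumed direction, the bias would not create a false positive, and that a sensitivity analysis could sit in an analysis plan that is not shown. Whether visits continue after withdrawal is different, because a later analysis plan cannot recover visits that did not take place.

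**Conclusion.** The concern holds as a conflict between stated rules. On the literal reading, that conflict causes outcome-related loss of week-4 SCORAD for patients rescued before week 4, loss of later assessments for every rescue user, and truncation of the levocetirizine amount. Exempting levocetirizine narrows the problem but does not remove it, because other emergency treatment still leads to withdrawal in a trial that promises to analyse everyone randomised. Imputation is a partial repair.

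The size cannot be determined. Observed-case power of 76% down to 61% and a shift of 0.25 to 3.0 points are what the assumed ranges produce; they are not estimates for this trial. The data loss itself depends on withdrawal meaning withdrawal from the study, which the article neither states nor excludes.

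**What to change.** 1. Reconcile Interventions, Secondary Outcomes and the Discussion so that one rule covers levocetirizine and other additional treatment. Which clinical rule applies is for the investigators.
2. State what withdrawal covers, and that stopping treatment or using additional treatment does not end study assessments. Keep the week 2, 4 and 8 assessments for all randomised patients, subject to their continuing consent.
3. In the intention-to-treat analysis, use the observed week-4 SCORAD regardless of rescue. Add one sensitivity analysis for rescue before week 4, for example counting it as no improvement.
4. Take the levocetirizine count from the concomitant-medication records already scheduled at weeks 2, 4 and 8.

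The cost is an amendment and one extra analysis, with no new visits. The article reports 30 of 60 participants enrolled as of June 2025, so an early change would still protect later patients' data; week-4 scores already missed cannot be recovered.
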